**Eligibility (see Section 3.0 for details)**

Patients who satisfy all of the following conditions will be eligible for this study:

- Biopsy proven cT1 and cT2 glottic carcinoma or carcinoma *in situ*
- Willing and capable to provide informed consent
- Signed study specific informed consent form
- Age > 18
- Eastern Cooperative Group (ECOG) Performance Status 0-1
- Appropriate staging studies identifying as AJCC stage 0 (Tis), I, or II true glottic vocal cord laryngeal cancer
- Agreement to use effective contraceptive methods such as condom/diaphragm and spermicidal foam, intrauterine device, or prescription birth control pills
- Patients with a history of non-head/neck invasive malignancies are eligible if they have been disease free for 3 or more years prior to entry into the study

## 1.0 BACKGROUND AND RATIONALE

### 1.1 Disease Background

Laryngeal cancer is the most common non-skin head and neck malignancy affecting approximately 13,000 patients annually in the United States. Over 75% of laryngeal cancers involve the true vocal cords or the glottic larynx, with over 90% of these cancers detected in early-stages (defined as carcinoma *in situ* and cT1-T2 tumors) when they are potentially curable by single-modality therapy. Local therapies are highly effective at curing early-stage glottic cancer, as rates of nodal involvement and metastatic disease are less than 5%. Treatment outcomes with radiation or surgical approaches for early-stage glottic laryngeal cancer yield local control rates for Tis and T1 tumors greater than 90%, and for T2 tumors 70-80%, and ultimate control rates exceed 90% after surgical salvage.

There are multiple voice-preserving local treatment options for early-stage glottic laryngeal cancer in the current National Comprehensive Cancer Network (NCCN) guidelines. These include conventional fractionated radiation therapy, CO2 laser excision, and hemilaryngectomy. Conventional radiation therapy of the larynx remains the most common treatment for Stage Tis, T1, and T2 glottic tumors typically delivered over 6 weeks to a dose of 62-70 Gy. Although functional voice outcomes from radiation therapy have historically been considered to be superior to surgery, daily radiation treatments over 6 weeks are inconvenient and unnecessarily irradiate large volumes of uninvolved normal tissue. The use of CO2 laser ablation has gained popularity for the treatment of Stage Tis or T1 lesions, which involves the removal of the gross tumor with a 2-3 mm margin thereby preserving the involved vocal cord and achieving good voice outcomes. Hemilaryngectomy is another voice preservation option particularly for selected Stage T2 lesions where the involved vocal cord and paraglottic space are removed, with additional resection of the ipsilateral arytenoid and/or anterior commissure if involved. Given the inconvenience of conventional radiation therapy, there is interest in developing hypofractionated stereotactic radiation approaches for early-stage glottic cancer to provide a non-invasive convenient treatment option.

Accelerated hypofractionated irradiation of early glottic cancer has been primarily used in Europe with results similar to conventional radiation therapy. Hypofractionated laryngeal irradiation was initially used during World War II due to a shortage of hospital beds. Even in this early experience with primitive radiation techniques, there was no difference in cure rates when reducing radiation therapy from a 5 week course to a 3 week course. Thereafter, the British Institute of Radiology Fractionation study for laryngeal and pharyngeal cancer showed equivalent survival rates and no significant differences in acute or long-term toxicity when comparing a 3-week or 6-week radiation course. In contemporary radiation practice, the Royal Marsden Hospital experience of 200 patients with T1 glottic cancer treated with accelerated radiation therapy to a dose of 50-52.5 Gy in 16 daily fractions, showed outcomes comparable to historical controls with a 93% 5-year local control rate and only a single severe toxicity occurring in a patient who continued to smoke more than 40 cigarettes per day during and after radiation treatment. In addition to patient convenience and cost-savings advantages, hypofractionated radiation therapy has the potential to further improve local control rates, especially as prolonged radiation courses are associated with lower local control and survival rates. A phase III clinical trial in Japan has also shown significantly improved local control in favor of hypofractionation when comparing 56.25 Gy in 25 fractions to conventional 60-66 Gy in 30-33 fractions in early-stage glottis cancer with equivalent minimal toxicity. These lines of evidence suggest that further hypofractionation has multiple potential benefits in early-stage glottic cancer including improved local control, cost savings, and patient convenience.

Given the success rates of local surgical treatments with CO2 laser ablation and hemilaryngectomy, there has been interest in developing hypofractionated hemilarynx stereotactic body radiotherapy (SBRT) treatment strategies for early-stage glottic cancer. SBRT has the potential to achieve excellent local control rates by delivering ablative tumor doses and to reduce acute and late radiation toxicities by geometrically sparing organs at risk (OAR) with steep radiation dose gradients. During respiratory motion, 4-D CT-scan analyses have shown the maximal movement of the vocal cords to be less than 1.3 mm, providing a feasible target for SBRT. Dosimetric analyses have also shown the sparing significant dose to pertinent organs at risk including the contralateral uninvolved vocal cord, arytenoids, swallowing muscles, strap muscles, carotid arteries, thyroid gland, and laryngeal skeleton using IMRT-based single cord irradiation. In particular, dose to the contralateral uninvolved vocal cord could be limited to less than 30 Gy which has the potential to improve functional voice outcomes. Based upon these dosimetric analyses, it was concluded that IMRT could be used to treat early-stage glottic tumors with 1-2 mm margins using ablative stereotactic radiation doses through single cord targeting. Presently, IMRT-based stereotactic hemilarynx irradiation protocols are under development in the Netherlands. Using CyberKnife radiation techniques, our dosimetric analyses suggest potential for even greater normal tissue sparing, and the potential for dose escalation or fraction reduction.

## 1.2 Study Agent(s) Background and Associated Known Toxicities

‘Stereotactic radiosurgery’ generally refers to a procedure design to treat deep-seated brain tumors or abnormalities, and is commonly performed on a specialized machine, such as the Gamma Knife. This procedure involves immobilizing the patient (cranial halo), affixing a stable 3-D coordinate system (fiducial box and head frame), performing high resolution imaging (CT or MRI), registering the images to the coordinate system using a computer, virtually simulating delivery of very focal and conformal dose profiles of radiation with steep dose gradients toward normal tissue, and finally carrying out the treatment with sub-millimeter accuracy. Typically very high doses of radiation (15-40 Gy) are given in a single treatment with this technique. Any adjacent normal tissues that receive this dose may be significantly damaged, thus the requirement for very conformal treatments with rapid dose fall-off. An alternate strategy has been to divide total radiation dose into two or three fractions, still with fairly large dose per fraction (6-10 Gy), attempting to decrease adjacent normal tissue toxicity. These fractionated techniques are referred to as ‘stereotactic radiotherapy,’ and are carried out with hope that surrounding normal tissue will tolerate the treatment as a result of relatively more successful sublethal damage repair as compared to tumor.

Translation of the stereotactic radiosurgery and radiotherapy concepts to extracranial sites has not been straightforward. With brain treatments, the skull serves as an excellent surface to rigidly couple the immobilization frame using stainless steel pins under local anesthesia. Once the skull is immobilized, targets within the skull are likewise immobilized in that there is very little movement of intracranial structures outside of fluid waves around the ventricles. Such is not the case for extracranial sites. Inherent motion, such as the heart beating, lungs expanding and emptying, and bowels churning, results in movement of potential targets. In addition, the external surface anatomy does not have structures amenable to rigid fixation to a frame. In 1994, Lax, et al, from the Karolinska Hospital in Sweden reported on the development and testing of an extracranial frame that incorporated a fiducial stereotactic coordinate system along its side panels. The system used vacuum pillows to make contact with three sides of the patient (maximizing surface area of contact) and correlation of external anatomical reference points on the sternum and calf for immobilization. To decrease respiratory excursion, an abdominal press was employed forcing the patient to perform relatively more chest wall rather than diaphragmatic breathing. A formal verification of reproducibility study was carried out, and

target motion was reduced to within 0.5 cm in the axial plane and 1.0 cm in the caudal/cephalad plane. With this degree of accuracy (compared to 0.05 cm target position accuracy for the Gamma Knife), stereotactic radiosurgery could not be performed; however, they did set up a program treating patients with extracranial stereotactic radiotherapy.

Stereotactic body radiation therapy (SBRT) is a new therapeutic paradigm for treating localized tumors outside of the central nervous system and involves delivering very high doses of focused radiation using unique beam arrangements and special immobilization equipment. As already demonstrated in lung and liver cancers, these treatments offer hope for improved local control of cancers that may translate into gains in survival especially for smaller early stage lesions. SBRT employs daily treatment doses dramatically higher than typical for conventionally fractionated radiation therapy (CFRT). In turn, it is incorrect to assume that SBRT radiobiology is similar to historical CFRT. Indeed, a unique biology of radiation response for very large dose per fraction treatments is being appreciated both in terms of tumor control as well as normal tissue consequences translating into unique clinical outcomes. For example, local control with CFRT in early stage lung cancer is consistently reported below 50% while several series using SBRT show local control around 90%.

SBRT has been defined by the American College of Radiology (ACR) and American Society of Therapeutic Radiology and Oncology (ASTRO) to involve the use of very large dose per fraction. Indeed, dose per fraction of 6 Gy minimum would obviously make SBRT very different from even the more abbreviated hypofractionation schemes described above. Typically, only 1-5 fractions are used for SBRT depending on the tolerance of adjacent or intervening normal tissues. Linear structures (like the spinal cord) and tubular structures (like the bowels) are commonly called “serially functioning tissues” akin to series electrical circuits because their function is disrupted if there is a defect anywhere along their pathways. It has been shown that serial functioning tissues are less tolerant to SBRT than so-called “parallel functioning tissues” like the peripheral lung and liver. In response, typically more fractions are employed (e.g., five fractions rather than one) when serially functioning tissue cannot be avoided.

Accuray’s Cyberknife system® is a 6 MV linear accelerator mounted on a robotic arm that is unconstrained by the gantry rotations of conventional linear accelerator radiotherapy systems. This allows for delivery of automated non-coplanar treatments and allows for increased conformality and dose gradient. The system also includes image guidance throughout the treatment using several available tracking systems that can track both bony anatomy or fiducial markers. These technologies make the Cyberknife system® ideal for delivering conformal high dose treatment plans while providing continuous image guidance and targeting corrections for quality assurance during treatment. The Cyberknife system® has been used in both intracranial radiosurgery and SBRT treatment of both lung and prostate.

### 1.3 Current Protocol

There are multiple therapeutic options for early-stage glottic larynx cancer with similarly high local control and overall survival rates as mentioned above. However, surgical approaches are invasive and may have worse voice outcomes, while conventional radiation therapy is inconvenient and treats large volumes of uninvolved normal tissue. Using CyberKnife-based SBRT, this protocol will spare adjacent uninvolved normal tissue for the purpose of decreasing the number of fractions required for curative treatment.

As surgical ablation and resection have excellent local control and cure rates for early stage glottis larynx cancer, the “radiosurgery” volumes will emulate volumes of tissue

typically removed or ablated during surgery. Thus, the radiation volume will approximate CO2 laser excision for carcinoma *in situ* and cT1 lesions which typically includes 2 mm of adjacent vocal cord, and the radiation volume for T2 lesions will emulate volumes of tissue typically removed during voice preserving hemilaryngectomy.

Through hypofractionated SBRT with geometric avoidance of uninvolved normal tissue, we aim to increase convenience, decrease toxicity, and improve local control compared to other methods of radiation treatment. As SBRT is a local treatment, eligible patients will be limited to early-stage laryngeal cancer defined as AJCC Tis, T1, and T2 lesions that have less than a 5% risk of nodal or distant metastases at diagnosis.

The feasibility of reducing fractions in early-stage laryngeal cancer has not previously been prospectively studied, and we will therefore conduct a careful phase I bio-equivalent dose fraction reduction study. Patients enrolled at each dose level will undergo routine evaluations to identify potential toxicities as well functional voice analyses. Adequate waiting periods will be used to ensure that fraction reduction does not proceed prior to observing toxicity. The purpose of the study will be either to determine the maximal fraction reduction possible until a dose is reached where a dose-limiting toxicity occurs. The initial dose and fractionation will be 50 Gy in 15 fractions with the goal to reduce number of fractions to a dose of 42.5 Gy in 5 fractions. The rationale for using 5 fractions is that it is tolerated in centrally located lung tumors at a dose of 50 Gy in 5 fractions, and thus, is likely to be tolerated in large caliber airways.

We hypothesize that the larynx has a similar radiation toxicity profile as the central lung airways and can be treated safely using 5 fractions. Potential dose limiting toxicity from this treatment will likely relate to voice hoarseness, stridor, or cough. Strict dosimetric guidelines to reduce the probability of toxicity will be used according to our institutional dosimetric analyses of CyberKnife larynx irradiation of anthropomorphic phantoms.

#### **1.4 Starting dose for Phase I study**

Previous experience in Europe suggests that the treatment of early-stage laryngeal cancer with 50-52.5 Gy in 16 fractions is safe and efficacious using conventional radiation techniques. Therefore, we hypothesize that with CyberKnife stereotactic radiotherapy techniques, that further fraction reduction is possible. The starting dose for this protocol will be similar to European protocols, and will be 50 Gy in 15 fractions daily. The current protocol will aim to reduce fractions while maintaining excellent local control and minimal toxicity that is seen with conventional radiation techniques.

#### **1.5 Voice Quality and Symptom Assessment**

In light of several recent reports describing the voice quality as measured by the Grade-Roughness-Breathiness-Aesthenicity-Strain (GRBAS), Voice Handicap Index (VHI), and various video stroboscopy techniques assessing laser resection and stripping, we will assess voice quality longitudinally as well through the use of VHI assessment. Due to inability to objectively evaluate voice through stroboscopy or other computer models, we will assess the voice quality subjectively via the VHI. The voice handicap index is a 30 question assessment evaluating the functional physical and emotional impact that voice handicap has on a patient. It is estimated that this form takes five minutes to complete.

In addition, we will assess swallowing function as measured by the MDADI (MD Anderson Dysphasia Inventory). This is a 20 question self-administered questionnaire designed to evaluate the impact of dysphasia on the quality of life of patients with head and neck cancer and it is estimated this form takes 5 minutes to complete.

## **1.6 Health Related Quality of Life**

With the establishment of the Patient Centered Outcome Research Institute (PRCORI) funded by the Patient Protection and Affordable Care Act, there is an increase interest in the impact of new treatment technologies on the quality-of-life, outcomes, clinical effectiveness and appropriateness of new technologies. Health-related quality of life (HR-QoL) or patient reported outcomes (PRO) are an important aspect of clinical outcomes. As such, there numerous studies reporting health-related quality of life in the management of early stage glottic carcinoma summarized in a recent systematic review of these studies evaluating radiotherapy and various surgical techniques including trans oral laser microsurgery or stripping. Unfortunately, there have been numerous health-related quality of life forms used to assess patients undergoing treatment for early-stage glottic cancer drawing conclusions between studies difficult. We will utilize the EORTC QLQ 30 and H&N35 which have been used in prior studies evaluating the treatment of early-stage glottic cancer. Additionally these forms are already in clinical use in our department as clinical practice.

To aid the ability to assess this technology from a cost-effectiveness standpoint will also assess patient preferences/utility of the treatment through the use of the Euro-QoL EQ 5D utility assessment. See section 1.7 regarding cost-effectiveness analysis.

## **2.0 STUDY OBJECTIVES**

### **2.1 Primary Objectives**

- 2.1.1 To determine the feasibility of fraction reduction for early-stage laryngeal cancer without exceeding the maximum tolerated dose.

### **2.2 Secondary Objectives**

- 2.2.2 To determine overall survival at 5 years.
- 2.2.3 To determine loco-regional control at 5 years as determined by physical exam, visualization of tumor by laryngoscopy, and CT-scan of the neck to determine if the primary tumor is controlled. A tissue biopsy or recurrent or persistent disease will be required to be considered a loco-regional failure.
- 2.2.4 To characterize functional voice quality of patients treated on this protocol.
- 2.2.5 To characterize the HR-QoL and PRO of patients treated on this protocol.
- 2.2.6 To determine cost-effectiveness of hypofractionated larynx irradiation.
- 2.2.7 To determine late toxicity as defined as treatment-related toxicity occurring  $\geq 18$  months from completion of radiation therapy.

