#### **4.11 Duration of Follow-Up**

Subjects will be followed for 5 years after completion of radiation therapy or until death, whichever occurs first. Subjects removed from treatment for unacceptable adverse events will be followed until resolution or stabilization of the adverse event. First follow-up after completion of treatment will occur at four weeks. Thereafter, protocol required follow-up in the Radiation Oncology Clinic or Otolaryngology Clinic will occur at every 3 months for the first year, every 6 months for the second year, and annually for years 3, 4, and 5 following treatment.

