#### **4.13 Subject Replacement**

Three subjects within dose levels -1 and 0 must be observed for 90 days before accrual to the next higher dose level may begin. For level 1, 7 patients must be observed for 90 days before accrual to the next higher dose level. If a subject is withdrawn from the study prior to completing therapy without experiencing a dose limiting toxicity prior to withdrawal, an additional subject may be added to that dose level. Subjects missing 3 or more radiation treatments due to toxicity will not be replaced since these subjects will be considered to have experienced a dose limiting toxicity.

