## **10.0 Statistical Considerations**

### **10.1 Primary endpoint**

The primary endpoint of this phase I clinical trial will be to either reach the minimum number of fractions that is tolerated for larynx irradiation or a dose of 42.5 Gy in 5 fractions whichever comes first. Patients will be treated in cohorts of 3-15. Toxicity will be graded using the National Cancer Institute (NCI) Common Toxicity Criteria for Adverse Events (CTCAE) version 4.0. A dose-limiting toxicity (DLT) is a grade 3 or greater toxicity definitely related to treatment in the following categories: laryngeal edema, voice, dyspnea, stridor, or cough. All reported DLTs will be verified by the study

chair, data monitoring committee, and as appropriate, independent review before final determination that a DLT has in fact occurred. The number of fractions will be reduced from 15, to 10 fractions, and then to 5 fractions (reduced by 5 fractions per step). The phase 1 portion of the study will be completed with either of the following events occur: 1) the MTD for a cohort is reached or 2) when the lowest number of fractions is treated and tolerated (42.5 Gy in 5 fractions).

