## 10.2 Phase 1 waiting periods

Fraction reduction for this phase 1 clinical trial will not occur until sufficient waiting has occurred after a cohort has been treated. A period of 90 days must pass before further fraction reduction for the purpose of assessing toxicity. If 90 days have passed without a DLT at a dose level, the trial will be allowed to the next level, so long as either criteria for defining the MTD or criteria for further fraction reduction is not reached. If the maximum number of patients are enrolled to a given fraction level, yet criteria for follow-up is not reached in a representative sample of patients, further enrollment to the protocol will be suspended until adequate follow-up is reached. No action will be taken for Grade 1 or Grade 2 toxicities. If any 2 Grade 3 toxicities occur within a dose level likely or definitely related to radiation therapy, the trial will be terminated with reporting of DLT at that dose level. Any Grade 4 or Grade 5 toxicity found to be likely or definitely related to treatment will result in termination of the trial with reporting of DLT at that dose level.

Grade 3 toxicities likely or definitely related to protocol therapy will result in action in schema provided below:

[figure not shown]

For level -1, if a Grade 3 toxicity occurs, the trial will be terminated with reporting of DLT.

For level 0, if a Grade 3 toxicity occurs, a step de-escalation will occur to level -1. If no grade 3 toxicities are experienced at level 0, the trial will proceed to level 1.

---

For level 1, if there are no Grade 3 toxicities after initial enrollment of 7 patients, an additional 8 patients will be enrolled. If there is no grade 3 toxicity after enrollment of an additional 8 patients, the trial will proceed to level 2. If there is a 1 grade 3 toxicity in the additional 8 patients, the trial will proceed to level 2 at the discretion of the PI and DSMC.

For level 1, if there is 1 Grade 3 in the initial 7 patient cohort, an additional 8 patients will be enrolled. If there is an additional Grade 3 toxicity at this level, the trial will be terminated with reporting of DLT. If there are no further grade 3 toxicities in the additional 8 patients, proceeding to the next level will be done at discretion of the DSMC and PI.

For level 1, if there are 2 grade 3 toxicities in the initial 7 patient cohort, the trial will be terminated with reporting of DLT.

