### **10.3 Secondary endpoints**

Secondary endpoints for the phase 1 portion of this study include local control, overall survival, functional voice quality, cost-effectiveness, quality of life, and late toxicity (defined as toxicities occurring > 18 months post-treatment).

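### Late toxicity is defined in two conflicting ways, and no named endpoint summarises lower-grade or non-DLT toxicity between day 90 and month 18

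*Protocol*

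**What the plan says.** **Late toxicity.** Protocol section 2.2.7 lists as a secondary objective "To determine late toxicity as defined as treatment-related toxicity occurring" at or beyond 18 months from the end of radiation. Section 10.3 lists "late toxicity (defined as toxicities occurring > 18 months post-treatment". The first includes month 18 and requires a link to treatment. The second excludes month 18 and requires no such link.

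**The 90-day gate.** Section 10.2 states: "A period of 90 days must pass before further fraction reduction for the purpose of assessing toxicity". It adds: "If 90 days have passed without a DLT at a dose level, the trial will be allowed to the next level". Section 4.13 sets the numbers to be observed: "Three subjects within dose levels -1 and 0 must be observed for 90 days before accrual to the next higher dose level may begin" and "For level 1, 7 patients must be observed for 90 days before accrual to the next higher dose level".

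**DLT.** Section 10.1 states: "A dose-limiting toxicity (DLT) is a grade 3 or greater toxicity definitely related to treatment in the following categories", and names laryngeal edema, voice, dyspnea, stridor and cough. Section 4.1 has a narrower definition: grade 4 or 5 only, in laryngeal edema, dyspnea or stridor. Neither gives an end date. The stopping rules in 10.2 (two related grade 3 events in a level, or any related grade 4 or 5 event) have none either.

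**Data collection.** After a four-week visit, section 4.11 schedules follow-up "every 3 months for the first year, every 6 months for the second year, and annually for years 3, 4, and 5". The table in section 5.4 places toxicity evaluation, including DLT, at follow-up visits, and TSH yearly. Section 5.1.8 requires acute as well as late events from the radiation to be reported and graded.

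**The concern.** A reader of the results will look for toxicity in two places: the DLT outcome that drives fraction reduction, and the late-toxicity endpoint. The waiting period is 90 days and the late endpoint opens at 18 months. Neither section 2.2 nor section 10.3 names a toxicity endpoint for the interval between them.

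The trial tests larger fractions, and section 9.1 accepts that hypofractionation may increase normal-tissue toxicity. A late-toxicity rate that leaves out related onsets between day 90 and month 18 could be read as more reassuring than the data the trial holds. The boundary conflict has a further effect: two analysts following different sections would report different late-toxicity counts from the same patients.

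**Working it through.** The protocol derives no figure on this point, so there is none to reproduce. The check sets the time windows side by side.

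**1. Length of the interval.** Inputs: 90 days (10.2, 4.13), 18 months (2.2.7, 10.3), five years of follow-up (4.11). With 365.25/12 days per month:
- 18 months = 18 × 30.44 = about 548 days
- 548 − 90 = 458 days, or 458/30.44 = 15.0 months
- 458/(5 × 365.25) = 0.25 of follow-up

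**2. Visits in it.** Counting from the end of radiation (an assumption about how 4.11 is read), visits after week 4 fall at months 3, 6, 9, 12, 18, 24, 36, 48 and 60. Months 6, 9 and 12 lie inside the interval. Month 3 (about day 91) sits at its lower edge. Month 18 counts as late under 2.2.7 but not under 10.3.

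**3. Where example events go.** All are treatment-related except the last.

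| Event | Late under 2.2.7 | Late under 10.3 | DLT or stopping rule |
|---|---|---|---|
| Grade 2 voice change, month 9 | no | no | no |
| Grade 2 hypothyroidism at first yearly TSH, about month 12 | no | no | no |
| Grade 3 stridor, definitely related, month 6 | no | no | DLT under 10.1, not under 4.1; counts toward the undated grade 3 rules of 10.2 |
| Grade 2 event, onset exactly month 18 | yes | no | no |
| Unrelated event, month 24 | no | yes | no |

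The first two rows show the gap, the third shows why it is not total, and the last two show the conflict between definitions.

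**4. The undated DLT.** The protocol does not say what follows if a DLT arises after day 90 in a level already cleared. Level 2 has no next level, so no 90-day gate applies to it, and section 10.1 gives no period over which it must be tolerated. The start of the 90 days is also loose: 10.2 runs it from when a cohort has been treated, and 4.13 gives no start.

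**5. Why the counting rule matters (illustration only).** The documents give no event rate or onset pattern, so both are assumed. Let q be the risk of a related grade 3 event by 18 months and s the share arising by day 90. A 15-patient level avoids the two-event rule with probability (1−p)^15 + 15p(1−p)^14, where p = q·s if only 90-day events count and p = q if events to 18 months count. For q = 10%, s = 50%: p = 0.05 gives 0.463 + 0.366 = 0.829, while p = 0.10 gives 0.206 + 0.343 = 0.549.

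| q | 90-day events only: s = 25% / 50% / 75% | Events to 18 months |
|---|---|---|
| 10% | 95% / 83% / 69% | 55% |
| 20% | 83% / 55% / 32% | 17% |
| 30% | 69% / 32% / 12% | 3.5% |

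These figures show how much depends on the unstated rule. They are not estimates for this trial and do not indicate which rule is right.

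**The case against.** A reader might infer that all treatment toxicity from month 3 to month 18 belongs to neither endpoint. The text does not support that. Ninety days is written as a minimum wait before the next level, not as the end of DLT observation. Neither DLT definition nor any stopping rule expires, and the schedule in section 5.4 continues DLT evaluation through follow-up. On the wording, a qualifying severe event at month 6 can still count toward the primary endpoint.

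Nor are the data lost. Adverse events are graded and reported under 5.1.8, and under section 6.0 the DSMC reviews serious events as they arrive and adverse events quarterly. A reader might also try to state what share of late events the endpoint misses. No such share can be given, because the documents contain no onset pattern.

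It can further be said that starting late toxicity at 18 months is an open choice, that the protocol nowhere defines late as beyond 90 days, and that tabulation of other events belongs in a statistical analysis plan. This stands in part: a rate counted from 18 months would be correct for its own definition, and a general adverse-event table may well be planned. It does not answer the conflict between 2.2.7 and 10.3, which lies in the protocol's own endpoint definitions. It also does not give grade 1–2 or non-DLT events in the interval a place in the listed endpoints.

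**Conclusion.** The point holds in a limited form. First, late toxicity has two incompatible definitions, differing in the boundary sign at a scheduled visit and in whether relatedness is required. This follows directly from the text. Second, between day 90 and month 18 (15.0 months, with the 6-, 9- and 12-month visits) no named endpoint summarises treatment-related toxicity, apart from events that meet the undated DLT or stopping rules. What is left out is grade 1–2 toxicity of any kind and events outside the DLT categories that trigger no stopping rule. The visit count assumes timing from the end of radiation. The number of events affected cannot be derived from the documents.

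The bearing of a DLT after day 90 on a cleared level is a separate omission in sections 10.1, 10.2 and 4.13. Overall this is a reporting weakness that should be corrected. It does not show that severe delayed toxicity would go uncounted.

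**What to change.** Use one definition in 2.2.7 and 10.3: treatment-related toxicity with onset more than 90 days after completing radiation, reported by dose level. Keep 18 months onward as a named sub-period, with the same boundary sign in both sections, so that the result now planned remains available. The cost is rewording two definitions. No visit or assessment is added, because toxicity is already evaluated at follow-up. The downside is that the headline late-toxicity rate will be higher than one counted from 18 months.

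Separately, reconcile 10.1, 10.2 and 4.13 so that they state whether a DLT after day 90 counts for a level already cleared, and from when the 90 days run. Reconcile the DLT definitions in 4.1 and 10.1 at the same time. Which rule to adopt is for the sponsor and the monitoring committee; this review does not prescribe one.
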